**Fig. 2 Fig2:**
[figure not shown]
Outline of the REVIVAL trial clinical protocol. Initially, patients will be informed about the clinical trial; if they accept and sign the consent, they will be randomized using the Sealed envelope® software. Group A will receive intranasal DXM; Group B will receive intravenous DXM. Both groups will be sampled on days 0, 3, 6, and 10 post-treatment to collect sera and nasopharyngeal swabs. Patients will be monitored throughout the study. The results will be tested for statistical differences between groups

Exclusion criteria include patients with an RT-PCR SARS-CoV-2 negative test; previously receiving GCs at high doses by oral or intravenous administration; severely immunosuppressed as in AIDS, pregnancy, and autoimmune diseases; those who have received outpatient treatment with steroids for more than 72 h before hospital admission; those older than 90 years; with DXM allergy; risk for glaucoma; or recurrent respiratory diseases. Patients receiving other monoclonal antibody-based treatments such as tocilizumab are also excluded. No other concomitant treatments are prohibited for patient eligibility.

Elimination criteria include voluntary withdrawing, lack of informed consent letter, or imminent risk of death within 48 h.

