**Methods:**

This is an approved open-label, multicenter, randomized controlled trial to compare the effectiveness of intranasal versus intravenous dexamethasone administered in low doses to moderate and severe COVID-19 adult patients. The protocol is conducted in five health institutions in Mexico City. A total of 120 patients will be randomized into two groups (intravenous vs. intranasal) at a 1:1 ratio. Both groups will be treated with the corresponding dexamethasone scheme for 10 days. The primary outcome of the study will be clinical improvement, defined as a statistically significant reduction in the NEWS-2 score of patients with intranasal versus intravenous dexamethasone administration. The secondary outcome will be the reduction in mortality during hospitalization.

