## Methods

### Trial design

The “REVIVAL” trial is an interventional, phase 2, multicenter, open-label, randomized controlled study in adult patients with confirmed COVID-19 diagnosis, designed to evaluate the efficacy (superiority) of low doses of intranasal DXM compared to intravenous administration (allocation ratio 1:1) in patients of five COVID-19 referral centers in Mexico City.

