#### Outcomes

The expected primary outcome is clinical improvement, defined as a two-point improvement in the ordinal scale regarding the initial NEWS-2 score. This is an adapted score recommended by the World Health Organization (WHO) and the National Institute for Health and Care Excellence (NICE) to facilitate the early recognition and escalation of deteriorating patients [55, 56]. Although this score is commonly adopted for triage, it can also be used for continuous assessment, particularly in predicting intrahospital mortality. In this context and based on previous experimental data regarding the sustained effect of intranasal dexamethasone, we decided to evaluate the improvement in the initial NEWS-2 score as the first outcome.

The secondary expected outcome includes a reduction in mortality that will be examined during treatment (after randomization), a reduction of the time required for mechanical ventilation, the length of patient’s stay in the hospital, 30-day post-discharge mortality, and intrahospital complications. Viral load, the immune-inflammatory profile, and other physiological parameters will also be evaluated before and after treatment (see above).

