#### Statistical analysis

Descriptive statistics using mean (standard deviation) or frequency (percentage) will be used following the dimension scale of the variable. An initial comparison between the hospital will define relevant differences among them. Since healthcare conditions are variable in each hospital included in this study, we will analyze the results with a multilevel mixed longitudinal model. The outcome analysis for NEWS-2 components (i.e., respiration rate, oxygen saturation, systolic blood pressure, pulse rate) will be done using the last observation carried forward (LOCF) in those subjects with at least two observations, this analysis will avoid over-optimistic estimates of efficacy. Other efficacy variables like biochemistry or cell counts will be analyzed without ITT due to the susceptibility to type II error.

Biochemical variables and cell counts will be aggregated using principal component analysis and use the scores if the Kaiser-Meyer-Olkin (KMO) is greater than 0.6 and sphericity *p* < 0.0001. The scores using varimax rotation will be used as dependent variables if the method is suitable for our data. The longitudinal mixed model can be described as:
$$ {y}_{ij}={X}_{ij}\beta +{u}_i+{v}_{j(i)}+{\epsilon}_{ij} $$

where *j* = 1,..,Ti are nested in 10 time points, within *i* = 1,..,5 hospitals. The Xs correspond to fixed variables like the treatments, age, sex, and weight, among other confounders.

A database in vertical format was reshaped to nest the biochemical, inflammatory markers, cell count adjusted by sex, age, and BMI. We will perform restricted maximum likelihood (REML) estimation in case we obtain balanced samples. However, if we obtain an unbalanced sample, we will use maximum likelihood instead [59]. Because we expect a small sample size from some hospitals, we will make inferences using the Kendward-Roger degrees of freedom method. We will make simultaneous inferences about l linear combinations of fixed factors. Despite the complicated situation where *l* > 1 we will consider:
$$ F=\frac{1}{l}{\left(\hat{\beta}-\beta \right)}^T\ L{\left({L}^T\ {\hat{\varphi}}_AL\right)}^{-1}\ {L}^T\ \left(\hat{\beta}-\beta \right) $$

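### The elimination rule for imminent death overlaps the mortality outcome, with its timing and analysis consequences unstated; separately, type II error is no valid reason to analyse biochemistry and cell counts without ITT

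*Protocol article*

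**What the plan says.** All references are to the Protocol article.

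- **Eligibility criteria (text after Fig. 2).** Three lists are given: inclusion, exclusion and elimination. The exclusion list opens with "Exclusion criteria include patients with an RT-PCR SARS-CoV-2 negative test" and does not mention imminent death. The third list reads: "Elimination criteria include voluntary withdrawing, lack of informed consent letter, or imminent risk of death within 48 h".
- **Fig. 2 legend.** Randomisation follows consent: "if they accept and sign the consent, they will be randomized using the Sealed envelope® software".
- **Trial design.** The trial is described as "interventional, phase 2, multicenter, open-label, randomized controlled study in adult patients with confirmed COVID-19 diagnosis".
- **Abstract, Methods.** "A total of 120 patients will be randomized into two groups (intravenous vs. intranasal) at a 1:1 ratio". On mortality: "The secondary outcome will be the reduction in mortality during hospitalization".
- **Outcomes.** Mortality is examined over the treatment period, after randomisation. Mortality at 30 days after discharge is also listed. The primary outcome is a two-point improvement in NEWS-2.
- **Procedures.** The case report form is filled in daily after randomisation and closed at end of treatment or at death, whichever is first.
- **Statistical analysis.** LOCF is used for the NEWS-2 components in patients with two or more observations. The next sentence says: "Other efficacy variables like biochemistry or cell counts will be analyzed without ITT due to the susceptibility to type II error".

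**The concern.** **Elimination rule.** Whether death is imminent is a forecast of an outcome that the trial counts. No threshold for it is given, and staff who make the judgement know the patient's arm. If the rule can be applied after randomisation and the patient then leaves the analysis, it takes out people shortly before they would count as deaths. Such patients are also unlikely to reach a two-point NEWS-2 improvement, so failures on the primary outcome would leave the denominator too. With 60 patients per group, a handful of removals moves the mortality result visibly.

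**Analysis without ITT.** This is a separate matter. The protocol gives fear of a type II error as its reason for setting ITT aside for variables that it calls efficacy variables. A concern about power does not justify leaving the comparison that randomisation protects, and the set to be used instead is not named.

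**Working it through.** **1. Timing of elimination, from the text.** Two features point to removal after entry: the list is separate from the exclusion criteria, and it contains voluntary withdrawal, which ordinarily happens after enrolment. One feature points the other way: a missing consent letter is a check made before randomisation, because consent comes first in Fig. 2 and in Data collection and management. The list therefore mixes timings. Removal after entry is the natural reading of the imminent-death item, but it is not stated.

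**2. Consistency with the outcome.** Procedures runs the case report form to death, and Outcomes counts deaths after randomisation. A rule that eliminates patients expected to die within 48 h pulls against both, unless it acts only before randomisation or leaves follow-up and analysis untouched. The protocol says neither.

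**3. Size, if eliminated patients leave the analysis.** The plan gives no mortality or elimination rate, so there is no plan figure to reproduce. The only input from the document is 60 patients per group; the rest is assumed.

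Assume a true mortality of 15/60 = 25.0% in both arms. Removing k patients who would die gives an observed rate of (15 − k)/(60 − k).

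- 6 versus 2 removed: 9/54 = 16.7% versus 13/58 = 22.4%; false difference 5.7 points.
- 6 versus 0 removed: 9/54 = 16.7% versus 15/60 = 25.0%; false difference 8.3 points.
- 6 versus 6 removed: 9/54 in each arm; no false difference, but 25.0% is reported as 16.7%.

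**4. Range over the assumptions.** With true mortality m in both arms and a share e of would-be deaths removed, the observed mortality is m(1 − e)/(1 − me). Type I error comes from 200,000 simulated trials per setting, 60 patients per arm, pooled z-test, critical value 1.96.

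| m | Shares removed | Observed mortality | False difference | Type I error |
|---|---|---|---|---|
| 20% | 50% vs 25% | 11.1% vs 15.8% | 4.7 points | 11.0% |
| 30% | 50% vs 25% | 17.6% vs 24.3% | 6.7 points | 13.3% |
| 40% | 50% vs 25% | 25.0% vs 33.3% | 8.3 points | 15.2% |
| 30% | 50% vs 0% | 17.6% vs 30.0% | 12.4 points | 33.0% |
| 30% | 50% vs 50% | 17.6% vs 17.6% | 0 | 5.1% |

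For example, at m = 30%: 0.30 × 0.50/(1 − 0.15) = 0.15/0.85 = 17.6%, and 0.30 × 0.75/(1 − 0.075) = 0.225/0.925 = 24.3%. With no removal the rejection rate is 4.9% to 5.2%.

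**5. Biochemistry and cell counts.** No arithmetic applies. The planned longitudinal mixed model is meant to cope with unbalanced data, so patients can stay in their allocated arm with whatever samples they have, and no values need to be carried forward. Setting LOCF aside for these variables therefore does not require setting ITT aside.

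**The case against.** The strongest reply is that the protocol nowhere says that randomised patients are removed, or that eliminated patients leave the mortality denominator. The consent item shows that at least part of the list works before randomisation, and elimination might mean only that study participation stops. Running the form to death and following mortality after discharge suggest that deaths are meant to be captured. Detailed handling of analysis sets often belongs in an analysis plan that is not shown. All of this stands as a limit on the point. It does not remove it, because the elimination rule is written text that conflicts with other written text, and nothing shown prevents its use after randomisation.

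On the second part, the ITT sentence directly follows the one on LOCF and may mean only that observed values are used without imputation. If so, the intended analysis may be close to the one proposed below. The stated reason would still be wrong, and the sentence as worded permits more.

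A reader might infer three stronger things that the document does not support:

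- That ITT is dropped for mortality. The sentence names biochemistry and cell counts only.
- That the biomarker set consists of survivors with samples. Samples are taken before treatment and at days 3, 6 and 10, and nothing says that earlier samples of patients who die are discarded.
- That the imminent-death item should simply become an exclusion criterion. That presumes an answer on timing which the sponsor has to give.

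**Conclusion.** The point holds in conditional form. The protocol contains an elimination rule that overlaps its mortality outcome, rests on unblinded judgement, and does not fit its own plan to follow patients to death. If eliminated patients leave the analysis, mortality is understated wherever the rule is used, and the comparison is biased when use differs between arms. Under assumed mortality of 20% to 40% and removal of 50% versus 25% of would-be deaths, the false difference is 4.7 to 8.3 points and the type I error 11% to 15%. These figures rest on assumed mortality and removal rates, since the document gives neither.

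A reader might conclude that randomisation is broken and mortality biased as a matter of fact. That goes too far: timing and removal from analysis are inferred, and equal removal under no true effect leaves the type I error at about 5%.

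Separately, and with no bearing on mortality, type II error is not a valid reason to leave the randomised comparison for biochemistry and cell counts.

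**What to change.** 1. **Reconcile the elimination criteria with Procedures and Outcomes.** State whether the imminent-death item applies only before randomisation. The clinical content of the rule is for the sponsor to settle.
2. **Fix the analysis consequence.** State that every randomised, consented patient stays in the mortality and NEWS-2 analyses in the allocated arm, that data are kept up to any withdrawal, and that vital status is followed where consent allows. The two-observation condition for the NEWS-2 components should be made consistent with this.
3. **Replace the sentence on ITT.** Suggested content: biochemistry and cell counts are analysed in all randomised patients with any sample, in the allocated arm, with the planned mixed model and without LOCF; a per-protocol analysis is a sensitivity analysis only.

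The cost is mainly protocol wording, plus follow-up of vital status where it would otherwise have stopped. The biomarker analyses may lose a little apparent sensitivity. The change is best made while recruitment is running, because follow-up lost on eliminated patients may not be recoverable later.

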### Interventions

#### Groups and comparators

The study will be carried out in two groups; group A (experimental) will receive intranasal DXM, and group B (Control) will receive intravenous DXM (Fig. 2). This experimental design is based on previously reported data indicating that intranasal administration can reach the brain and bloodstream quickly and efficiently [46–49]. Group A will receive intranasal DXM daily, at the dose of 0.12 mg/kg for the first 3 days, followed by 0.06 mg/kg for 7 days. Group B will receive 6 mg of intravenous DXM daily. In each hospital, the Pharmacovigilance staff will collect the adverse event information, for any (untoward o abnormal) medical manifestation, symptom, or disease, whether or not related with the drug treatment in each patient throughout the study.

#### Procedures

After randomization, a Case Report Format (CRF) (printed or electronic) for each patient will be filled daily by the medical staff and completed at the end of treatment or fatal outcome, whatever occurs first. Blood and saliva samples will be collected every third day during the whole treatment to perform ancillary tests such as SARS-CoV-2 viral load, functional immunological assessment (lymphocyte cytometry, cytokine/chemokine profile), and cortisol levels, among other analyses.

All biological samples will be each 48 h at every hospital center participant, transported by a specialized service and concentrated at Instituto de Investigaciones Biomédicas (UNAM) to be managed and stored at − 70 °C until use. As mentioned in the Informed Consent, all samples will be used for the next 3 years. Additional biological samples may be taken at each hospital center when necessary, according to the treating physicians and will not be part of this protocol.

All personal data and medical information of the patients will be treated in a strictly confidential way. Only the lead investigator and the hospital coordinator investigators will have access to this information.

#### Participants

The sample includes 120 adult patients of both sexes between 18 and 90 years of age, with moderate and severe forms of COVID-19. Participants are recruited from the five participant hospitals. Medical teams at each participating Hospital Center will be led by a responsible clinician who will obtain the informed consent letter. All eligible patients or a responsible family member (in the case that the patient cannot sign) receives an informed consent letter from the lead clinician, where the characteristics of the procedure are detailed. A medical team at each hospital will oversee the enrollment of participants according to a randomization scheme. A clinical monitor will supervise the data generation, protocol implementation, and appropriate patient enrollment.

#### Sample size and randomization

The analysts of the statistic team calculated the size with EPIDAT version 3.1.2 software, using the option “Sample size and surveillance curves” with an estimated 50% increase in the proportion of patients free of mechanical ventilation [intranasal DXM 70% vs. intravenous DXM 45%]. This value was estimated using the data of the COVID-19 patients registered in Mexican hospitals with a confidence of 95%, power of 80%, and proportion of losses of 10%. A sample size of 60 patients per group was obtained with these parameters. The randomization will be made with Sealed Envelope software. This software is freely available from https://www.sealedenvelope.com/simple-randomiser/v1/lists [Accessed May 5, 2020]. This study is a multicenter randomized controlled trial (Fig. 2).

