### Eligibility criteria

Inclusion criteria comprise patients of both sexes (non-pregnant female), aged from 18 to 90 years old, with presumptive SARS-CoV-2 infection and more than 5 days of clinical evolution, with moderate to severe symptoms requiring oxygen support or high flux mechanical ventilation (NEWS-2 ≥ 5), and abnormal CT-chest scan CO-RADS > 3. Patients should be diagnosed with atypical pneumonia, confirmed by chest images and oxygen saturation (SpO_2_) lower than 93% in ambient air or a ratio of the partial pressure of oxygen and the fraction of inspired oxygen (PaO_2_: FiO_2_) equal to or lower than 300 mmHg, and a positive RT- PCR SARS-CoV-2 test. These patients will be allocated into the experimental group or the control group in a 1:1 ratio (two arms) (Fig. 2) according to the randomization.

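### The 80% power is computed for freedom from mechanical ventilation, not for the NEWS-2 primary outcome, whose power is unstated

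*Protocol article*

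**What the plan says.** The only sample-size basis in the protocol article is in the section on sample size and randomization. The calculation uses "an estimated 50% increase in the proportion of patients free of mechanical ventilation [intranasal DXM 70% vs. intravenous DXM 45" per cent, "with a confidence of 95%, power of 80%, and proportion of losses of 10" per cent, and arrives at 60 patients per group.

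The Outcomes section defines the primary endpoint differently: "The expected primary outcome is clinical improvement, defined as a two-point improvement in the ordinal scale regarding the initial NEWS-2 score". The Abstract also puts NEWS-2 first, but as a reduction in score between routes of administration.

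The secondary outcomes are mortality during treatment, "a reduction of the time required for mechanical ventilation", length of stay, 30-day post-discharge mortality and in-hospital complications, with viral load, immune-inflammatory and physiological measures besides. The proportion of patients free of mechanical ventilation is in neither list. The article does not say that ventilation-free status stands in for NEWS-2, and it gives no NEWS-2 responder rate, mean difference, standard deviation or power.

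**The concern.** A power statement belongs to one endpoint, one assumed effect and one test. Here the endpoint and the effect are those of ventilation-free status, while the trial will be judged on NEWS-2. A two-point fall in NEWS-2 and staying off a ventilator are different events with different base rates, so 45% and 70% cannot be carried from one to the other.

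What is at stake is how the result is read. Trial design calls this a superiority study. A null result on NEWS-2 would be set against an 80% power that was never calculated for it. The Interim analysis section also allows the study to end if no trend is seen, and that decision is hard to interpret without knowing what NEWS-2 difference the trial can detect. In addition, the one effect that the trial was sized to find is not a named outcome, so nothing commits the investigators to reporting it.

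**Working it through.** **1. The plan's own figure.** Inputs from the section on sample size and randomization: rates 0.70 and 0.45, confidence 95%, power 80%, losses 10%. The allocation is 1:1 (Trial design). Sidedness is not stated; I take two-sided.

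Pooled two-proportion formula, with mean rate (0.70 + 0.45)/2 = 0.575:

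n = [1.960·√(2·0.575·0.425) + 0.842·√(0.70·0.30 + 0.45·0.55)]² / 0.25²
= [1.960·0.6991 + 0.842·0.6764]² / 0.0625
= 1.9395² / 0.0625 = 60.2, so 61 per arm before losses.

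Power for 70% vs 45% is 79.9% at 60 per arm, and 75.5% at 54 per arm (60 × 0.9). The stated 60 is thus recovered to within a patient or two. Other standard variants give other numbers, but each of them concerns ventilation-free status and none yields a power for NEWS-2.

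**2. The endpoints side by side.**

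| Role in the article | Variable | Type |
|---|---|---|
| Sample size | Free of mechanical ventilation | Proportion |
| Primary (Outcomes) | Two-point NEWS-2 improvement | Responder |
| Primary (Abstract) | Reduction in NEWS-2 score | Score |
| Nearest secondary | Time on mechanical ventilation | Duration |

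The sizing variable matches none of the other three rows.

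**3. What 120 patients could detect on NEWS-2 (illustration only).** The article gives no NEWS-2 inputs, so every control rate below is my assumption. Power = Φ{[d·√n − 1.960·√(2·p̄(1−p̄))] / √(p₁(1−p₁) + p₂(1−p₂))}, where d is the gain. This is an unadjusted two-sided 5% test. Each cell gives 54 / 60 per arm.

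| Control rate | +15 points | +20 points | +25 points |
|---|---|---|---|
| 50% | 35% / 38% | 57% / 61% | 77% / 82% |
| 60% | 38% / 42% | 62% / 67% | 84% / 88% |
| 70% | 46% / 50% | 75% / 79% | 94% / 96% |
| 75% | 54% / 58% | 84% / 88% | 98% / 99% |

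Worked cell (control 50%, +15 points, n = 54): p̄ = 0.575, so Φ[(0.15·√54 − 1.960·0.6991)/0.6910] = Φ(−0.388) = 35%.

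At control rates of 30% to 45%, a 25-point gain has about 75% to 80% power. The bottom right cell is a limit, because 75% + 25 points is a 100% response; above a 75% control rate a 25-point gain cannot occur.

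**4. If the primary is a mean score.** The detectable difference at 80% power is (1.960 + 0.842)·√(2/n): 0.54 SD at 54 per arm and 0.51 SD at 60. Baseline adjustment lowers it. With an assumed baseline correlation of 0.5, the factor is √(1 − 0.25) = 0.866, which gives 0.47 and 0.44 SD.

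**The case against.** **The calculation is not the planned analysis.** The Statistical analysis section plans a multilevel longitudinal mixed model with covariates and repeated measurements, and carries the last observation forward for the NEWS-2 components. A single-time, unadjusted comparison is only a stand-in: the model may be more efficient, and more than 54 per arm may be retained. This stands, and it is why the figures above are an illustration. It does not cure the mismatch, since the article gives no inputs for the model's power either.

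**A related outcome is listed.** Time on mechanical ventilation is a secondary outcome, and the software option named, "using the option “Sample size and surveillance curves", appears to be one for survival curves. So ventilation is not absent from the outcomes. But a duration is not the proportion free of ventilation, and it is not primary.

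**A reader might infer that the true power is far below 80%.** The documents do not support this. No NEWS-2 control rate or effect is given, and in the table several cells exceed 80%. Nor does a high control rate by itself lower power: over 50% to 75%, power at a fixed gain rises, and a high rate only caps how large the gain can be.

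**A reader might also infer that some patients are ventilated at entry and so can never count as free of it.** The eligibility wording, "requiring oxygen support or high flux mechanical ventilation", is ambiguous and may mean high-flow oxygen. The point does not depend on it.

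**This is a phase 2 trial, already recruiting, with its size fixed.** That is true, and it limits the remedy to correct labelling and disclosure. It does not make the present power statement apply to the primary outcome.

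**Conclusion.** The point holds: the 80% power is a property of a 70% vs 45% comparison of ventilation-free status, and the power of the NEWS-2 primary comparison is unstated. This rests on the text alone and does not depend on which sample-size formula was used. Nor is it a detail left to an analysis plan, because the article states both the sizing endpoint and the primary endpoint, and they differ.

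Its size can only be shown as a range. Under assumed control rates of 50% to 75%, an unadjusted two-sided 5% test and 54 to 60 per arm, power is about 35-58% for a 15-point gain, 57-88% for 20 points and 77-99% for 25 points. For a mean score, the detectable difference is about 0.51 to 0.54 SD, and smaller with baseline adjustment. The conclusion is that the power is unknown, not that the trial is underpowered.

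**What to change.** In the section on sample size and randomization:

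- Say that the 80% refers to the proportion free of mechanical ventilation.
- Give the power, or the minimum detectable difference, of the fixed 120 patients for the NEWS-2 primary outcome under its planned analysis. Label the assumed control rate or standard deviation as assumptions, and show a short table over plausible values.

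In the Outcomes section, list the proportion free of mechanical ventilation, as used in the calculation, as a secondary outcome. Alternatively, justify in the sample-size text why it is the sizing basis for a trial whose primary outcome is NEWS-2.

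The cost is about a paragraph and, if the outcome is added, one further secondary analysis. The stated power may become less favourable. No extra patients are needed.

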The internal random structure [$$ {L}^T\ {\hat{\varphi}}_AL $$] can change in different settings, but still will be a good approximation. Simulations studies showed adequate performance of modifications with different REML [60]. Finally, the structure of residual error will be analyzed within the lowest-level group. Once recognized, the covariance structure we will use unstructured, Toeplitz, or exponential corrections. This approach will give unbiased approximation even in presence of unbalanced samples.

The residuals for our mixed models will be considered by the source of present variability: The marginal residuals will predict the marginal errors, the conditional residuals, and the best linear unbiased predictor (BLUP) residuals. The conditional residuals will be standardized with:

$$ {\hat{\varepsilon}}_k^{\ast }=\frac{{\hat{\varepsilon}}_k}{\sigma\ \sqrt{p_{kk}}} $$ , where *p*_*kk*_ represents the *k*th element of the covariance structure. These residuals are functions of the joint leverage of fixed and random effects.

Subgroup analysis will be based on interaction as secondary analysis. This information will help to identify multiplicative effects from basal conditions like the presence of type 2 diabetes, obesity, hypertension, clinical history IECA medication, or other conditions.

All analysis will describe the number of patients with the outcome of interests, the treatment effect (mainly using eta squared), additive and multiplicative interactions with 95% confidence intervals, and the direction of the interaction (positive or negative) by specific subgroups. The analysis will be performed with Stata version 17.0 [StataCorp LLC College Station TX]. A statistical difference with *P* < 0.05 will be considered significant.

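### The 60 patients per group match the two-proportion size before the stated 10% losses; if lost patients drop out of the analysis, power is about 75%, not 80%

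*Protocol article*

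**What the plan says.** The Protocol article, under Sample size and randomization, gives one calculation. Its effect is "an estimated 50% increase in the proportion of patients free of mechanical ventilation", with the rates in brackets as 70% for intranasal and 45% for intravenous dexamethasone. The other inputs are "confidence of 95%, power of 80%, and proportion of losses of 10" (per cent). The result follows directly: "A sample size of 60 patients per group was obtained with these parameters". The Abstract and the Participants section give 120 as the total, so 60 per group is the number to be randomised, not an evaluable number still to be inflated.

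The software is named as EPIDAT, with an option whose title mentions curves. The formula, the sidedness and the size before losses are not given. Under Statistical analysis the article says: "A statistical difference with *P* < 0.05 will be considered significant". That section describes longitudinal mixed models and no time-to-event method.

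**The concern.** The article prints both the inputs and the result, so the sum can be checked without an analysis plan. The stated 60 is what the usual formula returns when the 10% losses are left out, although losses are listed among the parameters that produced it. If so, the trial as sized has less power for its sizing outcome than it claims. This calculation is also the only justification the article gives for 120 patients.

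The effect is described inconsistently as well. Moving from 45% to 70% is a rise of 25 percentage points, and 70/45 = 1.556, a relative increase of 56%. It is not 50% on either scale.

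**Working it through.** **Inputs from the article:** p1 = 0.70, p2 = 0.45, difference 0.25, 80% power, 10% losses, 1:1 allocation. **Assumption:** two-sided 5%, the usual reading of 95% confidence with P < 0.05. Then z(0.975) = 1.960, z(0.80) = 0.842 and the mean rate is 0.575.

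**1. Size before losses (pooled two-proportion formula)**

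n = [1.960 × √(2 × 0.575 × 0.425) + 0.842 × √(0.70 × 0.30 + 0.45 × 0.55)]² / 0.25²
= (1.3702 + 0.5693)² / 0.0625 = 60.2, rounded up to 61.

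This is where the plan's 60 reproduces. Power at 60 evaluable per group is 79.9%.

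**2. Size after losses**

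60.2 / 0.9 = 66.9, so 67 per group (61 / 0.9 = 67.8, so 68, if rounded at each step). The total would be 134 to 136.

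**3. Power of the design as printed, lost patients removed**

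Evaluable per group: 60 × 0.9 = 54.
z = (√54 × 0.25 − 1.3702) / √0.4575 = 0.690, so power is 75.5%. The exact power of the uncorrected chi-square test at 54 is 74.7%.

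**4. Other two-sided formulas, lost patients removed**

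| Method | n per group before losses | after dividing by 0.9 |
|---|---|---|
| Pooled | 60.2 | 66.9 |
| Unpooled | 57.5 | 63.8 |
| Arcsine | 60.0 | 66.6 |
| Continuity-corrected | 68 | 76 |
| Log-rank, Schoenfeld | 56.9 | 63.2 |
| Log-rank, Freedman | 63.1 | 70.1 |

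The log-rank rows use HR = ln 0.70 / ln 0.45 = 0.447 and a mean event proportion of 0.425. None of the after-loss figures is 60. Multiplying by 1.1 instead gives no less than 62.6. Log-rank power at 54 per group is 77.9% (Schoenfeld) or 73.6% (Freedman).

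**5. Log-rank with losses as censoring**

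Assume exponential event times and 10% exponential loss over follow-up, so a lost patient counts until leaving. The event proportions become 0.286 and 0.526, mean 0.406.

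- Schoenfeld: 48.34 events / (2 × 0.4056) = 59.6, so 60 per group. Power at 60 is 80.3%; simulated log-rank power is 79.4% to 79.6%.
- Freedman: 53.65 events / (2 × 0.4056) = 66.1 per group. Power at 60 is 76%.

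**6. One-sided 5%, lost patients removed**

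The plain formula gives 48 before and 54 after losses. With continuity correction it gives 55 and then 61 to 62.

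**The case against.** The strongest defence is step 5. The named software option points to a comparison of curves, and in such a comparison lost patients are censored, not deleted. A Schoenfeld log-rank with 10% censoring returns 60 per group, and simulation supports about 80% power. A reader might therefore go too far in concluding that no log-rank version can yield the printed number, or that the stated 80% is certainly false. The documents do not support that: the software routine is not shown, and one standard two-sided calculation does reach 60 with losses included.

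This stands as a possibility, with limits. It needs a censoring model the article never states. The Freedman formula under the same censoring still needs about 66. And the Statistical analysis section describes no time-to-event comparison of ventilation, so the power of a log-rank test would belong to a test that is not described.

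A one-sided test with continuity correction also comes near 60, but nothing in the article points to it.

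Two further inferences should be resisted. One is that the worded 50% increase means a target of 67.5%, which would enlarge the shortfall; the rates 70% and 45% are printed explicitly, so the wording is loose and the rates govern. The other is that a null result on the primary outcome would be judged against a wrong power. The primary outcome is NEWS-2, and neither 80% nor 75% describes it.

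**Conclusion.** The point holds in moderate form. For a two-sided two-proportion comparison with lost patients removed, 60 per group is the size before losses. The stated inputs call for about 67 to 68, and the design as printed has about 75% power. That is about 5 points below the claim: the chance of missing the assumed effect is about 25% instead of 20%. Among the two-sided calculations tried, only the Schoenfeld-type log-rank with censored losses supports the printed figure.

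The conclusion rests on a two-sided 5% level, on the printed rates, and on 10% of patients contributing nothing to the comparison. It does not invalidate the trial and says nothing about power for NEWS-2. The 50% wording is a separate, smaller error in the same sentence and holds whichever formula was used.

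**What to change.** Keep 120 patients and correct the Sample size and randomization section:

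- State the test, the sidedness and how the 10% losses enter.
- Check the software run. Unless it is confirmed as a log-rank calculation with censored losses, and that test will also be the analysis, restate the result along these lines: *60 randomised per group, 54 evaluable after 10% losses, give about 75% power (two-sided 5%) for 70% against 45%.*
- Describe the effect as 25 percentage points (56% relative).
- Say that this power refers to freedom from mechanical ventilation and not to the NEWS-2 primary outcome.

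The cost is a few sentences and possibly a less favourable stated power. No patients are added and no procedure changes.
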